## Abstract

**Background:**

Early-onset Group B haemolytic streptococcus infection (EOGBS) is an important cause of neonatal morbidity and mortality in the first week of life. Primary prevention of EOGBS is possible with intra-partum antibiotic prophylaxis (IAP.) Different prevention strategies are used internationally based on identifying pregnant women at risk, either by screening for GBS colonisation and/or by identifying risk factors for EOGBS in pregnancy or labour. A theoretical cost-effectiveness study has shown that a strategy with IAP based on five risk factors (risk-based strategy) or based on a positive screening test in combination with one or more risk factors (combination strategy) was the most cost-effective approach in the Netherlands. IAP for all pregnant women with a positive culture in pregnancy (screening strategy) and treatment in line with the current Dutch guideline (IAP after establishing a positive culture in case of pre-labour rupture of membranes or preterm birth and immediate IAP in case of intra-partum fever, previous sibling with EOGBS or GBS bacteriuria), were not cost-effective. Cost-effectiveness was based on the assumption of 100% adherence to each strategy. However, adherence in daily practice will be lower and therefore have an effect on cost-effectiveness.

**Method/Design:**

The aims are to: a.) implement the current Dutch guideline, the risk-based strategy and the combination strategy in three pilot regions and b.) study the effects of these strategies in daily practice. Regions where all the care providers in maternity care implement the allocated strategy will be randomised. Before the introduction of the strategy, there will be a pre-test (use of the current guideline) involving 105 pregnant women per region. This will be followed by a post-test (use of the allocated strategy) involving 315 women per region. The outcome measures are: 1.) adherence to the specific prevention strategy and the determinants of adherence among care providers and pregnant women, 2.) outcomes in pregnant women and their babies and 3.) the costs of each strategy in relation to the effects.

**Discussion:**

This study will provide recommendations for the implementation of the most cost-effective prevention strategy for EOGBS in the Netherlands on the basis of feasibility in daily practice.

**Trial registration:**

Dutch Trial Register, NTR3965

## Background

Vertical transmission of the group B haemolytic streptococcus (GBS) during delivery is the main cause of neonatal infection in the first week of life and it leads to early-onset Group B haemolytic streptococcus disease (EOGBS). EOGBS is an important cause of perinatal mortality, serious illness and long-term effects for the baby [1,2]. The mortality rate for children with EOGBS varies from 9.0 to 10.3% [3-5].

Estimates of the incidence of EOGBS vary between 0.23 and 1.22 per 1000 live births in several European countries and the USA [6-14]. The estimated incidence of EOGBS in the Netherlands is based on proven (0.36 per 1000 live births) [13] and probable EOGBS cases and is 1.9 per 1000 live births [1].

Because of the severe consequences, the importance of the prevention and mitigation of EOGBS is widely recognised. Primary prevention of EOGBS is possible with intra-partum antibiotic prophylaxis (IAP) for pregnant women who are GBS carriers. Different prevention strategies are used internationally based on identifying mothers at risk, either by screening for maternal colonisation with GBS during pregnancy or by identifying risk factors for EOGBS in pregnancy or during labour. Established risk factors include the pre-labour rupture of membranes (> 18 hours), intra-partum fever (≥38.0°C), preterm birth (<37 weeks), GBS bacteriuria in current pregnancy and a previous sibling with EOGBS.

However, none of the preventive EOGBS strategies in place at present result in the complete prevention of EOGBS, either because the strategy is not fully effective in itself, or because it has drawbacks which may result in non-adherence by both care providers and pregnant women.

1. In the risk-based strategy, all women with one or more of the established risk factors for EOGBS receive IAP. Care providers are clear about how to apply this strategy. The effect of the strategy is limited because over 40% of babies who develop EOGBS are born to mothers without a risk factor during pregnancy or labour [13].

2. In the screening strategy, a culture is taken at 35–37 weeks of gestation, and all GBS-colonised women receive IAP. As with the risk-based strategy, care providers understand clearly how to apply this strategy, which is affected by two problems: 1. the failure of the laboratory to detect GBS in pregnant women accurately accounts for a consistent proportion of EOGBS cases [6,15-18] and 2. the large numbers of women receiving IAP and the possible negative side-effects such as antibiotic resistance [6].

3. In the combination strategy, a culture is taken at 35–37 weeks of gestation and women with both GBS colonisation and one or more of the established risk factors for EOGBS receive IAP. This strategy leads to the most accurate use of IAP and therefore results in the lowest rate of negative side-effects. However, persistent problems are that laboratories fail to detect GBS in pregnant women accurately [6,15-18] and over 40% of babies who develop EOGBS are born to mothers without a risk factor during pregnancy or labour [13]. Furthermore, adherence to this strategy may be affected by awareness among care providers and pregnant women of GBS colonisation and this could lead to an increase in IAP, even in the absence of risk factors.

4. The current Dutch guideline, which was issued in 1998 [19], prescribes IAP for women with intra-partum fever, a previous sibling with EOGBS or GBS bacteriuria during current pregnancy. Cultures are taken in cases of pre-labour membrane rupture or preterm birth and IAP is given if GBS colonisation is established. One of the problems with the Dutch guideline is that culture results take up to 72 hours to deliver and cultures are therefore often not yet available when labour starts. IAP in response to a risk factor is therefore predominantly based on clinical observation. The problems mentioned above – the inaccurate detection of GBS in the combination strategy [6,15-18] and the fact that over 40% of babies who develop EOGBS are not born to mothers with risk factors [6]– are also applicable to the Dutch guideline. 

The effect of the introduction of the Dutch guideline on the prevention of EOGBS was first evaluated in 2007 [13]. Trijbels et al. reported that the incidence of neonatal GBS disease fell hardly at all after the introduction of the guideline and recommended a change to the national guideline. In 2005, Van den Akker et al. compared the cost-effectiveness of the Dutch guideline with the risk-based strategy, the screening strategy and the combination strategy in a theoretical model [20]. This analysis took into account the unique maternity care system in the Netherlands, which involves a 31% home birth rate and a stratified care model with different professional care providers at different risk levels. It found that, assuming 100% adherence by care providers and clients, the combination strategy and the risk-based strategy would have the most favourable cost-effectiveness ratios. The screening strategy was the most effective, but the least cost-effective strategy, whereas the Dutch guideline had less effect but involved even higher costs.

However, the actual impact of any of these four strategies will be the product of efficacy (in other words, to what extent can the strategy prevent EOGBS?) and the level of implementation (the extent to which the strategy is followed by all care providers and all pregnant women). Full adherence is unlikely in daily practice. There are many reasons why care providers cannot always observe guidelines: time constraints, lack of patient cooperation, lack of self-efficacy, difficult logistical procedures or even a lack of clear procedures in the guideline, to name just some examples [21-24].

In 2012, there was a study analysing the determinants of the uptake of the four GBS prevention strategies in the Netherlands mentioned here. The study looked at care providers and pregnant women by means of focus group interviews and a subsequent questionnaire study. As well as identifying the determinants associated with each prevention strategy, the study found room for improvement in adherence to the current Dutch guideline, especially in the assessment of clinical risk factors and the process of culture taking. Furthermore, there was not enough support for the introduction of the screening strategy. This strategy also turned out not to be cost-effective in the theoretical model and so it was decided not to introduce this strategy in the Netherlands.

The aim of our study is to implement the current Dutch guideline, the risk-based strategy and combination strategy, and to study the effects in daily practice.

Our results will support recommendations for the national implementation of the most cost-effective EOGBS prevention strategy on the basis of feasibility in daily practice.

The research questions are:

a. What are the levels of adherence to each prevention strategy and the determinants of adherence among care providers and pregnant women?

b. What are the outcomes in pregnant women and their babies?

c. What are the costs of each prevention strategy and how do they relate to the effects?

## Methods/Design

### Innovation framework

In the present study, we use a framework based on several theories that have proven useful in the past for the introduction and evaluation of innovations – such as guidelines – in a wide range of settings in Dutch health care [25-30].

Figure 1 shows the four main stages in innovation processes. In the dissemination stage, the innovation should reach every professional. In the adoption stage, the professional develops positive or negative intentions about using the innovation. In the implementation stage, the professional tries to use the innovation in daily practice and finds out what working with the innovation actually means. In the final stage, the continuation stage, working with the innovation either becomes routine practice or not.

**Figure 1 F1:**
[figure not shown]
**Framework representing the innovation process and related categories of determinants **[23]**.**

These four main stages in innovation processes can be thought of as success or failure points at which the desired change may, or may not, occur. The transition from one stage to the next can be affected, positively or negatively, by various determinants (see Figure 1). Determinants can be broken down depending on their association with:

1. The innovation (determinants such as complexity, relative advantage, compatibility),

2. The adopting person (determinants such as outcome expectations, self-efficacy, perceived patient cooperation),

3. The organisation (determinants such as staff turnover, financial resources, available time),

4. The socio-political context (determinants such as legislation) [23,24].

A detailed understanding of determinants helps to design an innovation strategy that can achieve real change [23,31-33]. A determinant analysis was performed in 2012 (see Background), resulting in a set of determinants that the present study will anticipate (see Activity 1).

#### The Dutch maternity care system

The Dutch EOGBS guideline targets obstetricians, midwives and paediatricians working in the Dutch maternity care system. This system is a stratified care model with different professional care providers at different risk levels. Midwives working in primary care are the main group of caregivers in low-risk pregnancies. Obstetricians and midwives working in hospitals take care of medium- or high-risk pregnancies and births. Care pathways are organised in Obstetric Collaboration Groups (OCGs). An OCG is organised around a hospital and consists of midwives (with independent practices and/or hospital-based), obstetricians and paediatricians. The OCGs make agreements about the regional organisation of maternity care and interdisciplinary collaboration.

### Overview of project

This project comprises two main activities: 1). the development and application of innovation strategies to enhance the uptake of the three prevention strategies in three study regions and 2). the study of the effects of the implementation. Before the introduction of the three prevention strategies in August 2013, a pre-test will be conducted over a period of three months (March-May 2013). Then, over a period of two months, implementation activities will take place (June-July 2013). To assess the effect of the implementation, a post-test will be performed over a period of six months (August 2013-January 2014).

### Activity 1: Development and application of innovation strategies

#### Participants

Three OCG regions will be recruited. Each OCG consists of one hospital working with three to five midwifery practices. The EOGBS prevention strategy to be implemented – the Dutch guideline, the risk-based strategy or the combination strategy – will be randomly allocated to each region.

All the respondents who participated in the previously performed determinant analysis (see Background) will be asked if their OCG is interested in participating in the study. All the care providers who respond positively will be approached. The chairpersons of the OCGs in the region will then be contacted. If participating members of the OCG express interest, the region will be informed about the study protocol in an OCG meeting. Inclusion criteria for participation are:

a. All OCG members have to participate in the study as the prevention strategy will be implemented in the entire region. If, for example, one member in the OCG does not initially support the allocated prevention strategy, this will have a direct effect on implementation and the cost-effectiveness.

b. The OCG must consist of one hospital and three to five midwifery practices in primary care in the vicinity. The number of care providers participating will be approximately ten midwives in primary care, five obstetricians, eight to ten hospital-based midwives and five paediatricians.

c. The OCG must consider collaboration between the professionals to be good.

#### Innovation strategies

##### 1. Providing information (enhancing dissemination and adoption)

To enhance awareness of the allocated prevention strategy, all the care providers will receive a personal letter and the project will be discussed at several regular meetings of the OCG. Furthermore, a patient information brochure about the prevention strategy will be developed for distribution by all care providers to their clients.

##### 2. Recruitment of coordinators (enhancing adoption, implementation and continuation)

Two implementation coordinators will be assigned to each participating OCG: a midwife and an obstetrician who introduce and guide, coordinate and monitor the implementation process for the allocated prevention strategy. The coordinators will receive coaching throughout the project from an implementation expert and the project group.

##### 3. Training of professional care providers (enhancing adoption and implementation)

Before the introduction of the prevention strategy in August 2013, all care providers will receive training with the aim of optimising the implementation process. The training will be based on the determinants identified in the determinant analysis performed in the past. The training consists of three components:

a. General information will be provided about the theoretical background to EOGBS and its prevention. There will be a particular focus on correct culture-taking since considerable variation was found among care providers in the determinant analysis. The aim is to train all care providers to the same level.

b. The allocated prevention strategy, and the study protocol, will be discussed in detail. Potential barriers to adherence will be discussed and particular attention will be paid to logistics. The aim is to clarify and standardise the allocated strategy for the EOGBS prevention.

c. There will be a particular focus on counselling for pregnant women, emphasising clear and unambiguous information about the screening procedure, the consequences, the administration of IAP and shared decision-making about treatment options.

### Activity 2: Study of the effects of the implementation of each prevention strategy

#### Participants and study design

Before the actual introduction of the three prevention strategies in August 2013, a pre-test will be conducted over a period of three months to assess adherence to the current Dutch guideline. To determine the effects of the implementation of the three strategies, a post-test will be performed over a period of six months. During both the pre-test and post-test, all midwives and obstetricians will prospectively register all pregnant women from 30 weeks of gestational age onwards. All pregnant women will receive information about the EOGBS prevention strategy in their region and permission is acquired on the basis of opting out [34]. Women who decline to participate will be treated in accordance with the current Dutch guideline. However, pregnant women will be explicitly asked for permission to take cultures (see outcome measures) and for IAP in line with the usual professional standards. Therefore written informed consent will be obtained from all pregnant women.

#### Sample size

To determine adherence to each strategy with sufficient precision, 315 women are needed (in the case of 70% adherence, the 95% confidence interval will be 65-75%) since this number will ensure statistical significance at a variation in adherence of 10% between strategies (alpha = 0.05, power = 80%).

The pre-test must include 105 pregnant women per region: 315 in total for the three regions. The post-test must include 315 pregnant women per region: 945 in total for the three regions.

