#### Adherence and determinants of adherence

##### Adherence

Throughout the study period, adherence to the key components of each prevention strategy will be measured for all care providers on the basis of the medical records of all the pregnant women. During the pre-test, adherence to the current Dutch guideline will be measured, and adherence to the allocated prevention strategy will be measured during the post-test. The key components are: assessment of the clinical risk factors for EOGBS, culture-taking during pregnancy and during labour, IAP during labour and treatment of the baby. In this way, the level of adherence will be measured as the proportion of all prescribed activities the professional has actually applied: “completeness of use”. The medical record search will be performed using standardised registration forms. Only the combination strategy requires a recto-vaginal culture to be taken from pregnant women between 35 and 37 weeks by their care provider. In all prevention strategies the care provider decides whether IAP is necessary or where there is a contra-indication for antibiotic prophylaxis.

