#### Analysis

Data will be analysed according to the intention to treat principle. OCGs will be analysed on the basis of the allocated strategy, regardless of whether the strategy is fully implemented in the OCG. Base characteristics will be described. The differences in the outcome percentages for the pre-test and the post-test will be calculated and included in the cost-effectiveness analysis. Descriptive and regression techniques will be used to evaluate the effect of the implementation.

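### The 65–75% interval and the 80% power both assume 315 independent women, although adherence is what some 23–30 professionals in four to six units per region do

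*Protocol article*

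**What the plan says.** Under Sample size (Activity 2), the protocol article gives the precision as "in the case of 70% adherence, the 95% confidence interval will be 65-75" per cent. It adds that "this number will ensure statistical significance at a variation in adherence of 10% between strategies", with "alpha = 0.05, power = 80" per cent. The number is then fixed: "The post-test must include 315 pregnant women per region: 945 in total for the three regions". No design effect or ICC is mentioned.

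Under Adherence, "adherence to the key components of each prevention strategy will be measured for all care providers" from the women's records, and "the level of adherence will be measured as the proportion of all prescribed activities the professional has actually applied". Under Participants (Activity 1), each region is one hospital with three to five midwifery practices, and "The number of care providers participating will be approximately ten midwives in primary care, five obstetricians, eight to ten hospital-based midwives and five paediatricians". The section on training of care providers says that the earlier determinant analysis found considerable variation between providers in how cultures are taken. The Background ends with the aim of supporting a national recommendation. Of the modelling, the Analysis section says: "Descriptive and regression techniques will be used to evaluate the effect of the implementation".

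**The concern.** A binomial interval for 315 women is valid only if one woman's adherence result tells us nothing about the next woman's. Here the measured behaviour belongs to the professional, and each professional or unit treats many of the women. If providers differ, the 315 records carry less information than 315 independent observations. The study's own rationale, which includes a questionnaire on the determinants of use among providers, presupposes that they do differ.

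Two stated properties of the design are at stake: the ±5-point precision for each strategy and the 80% power for a 10-point difference. The adherence estimates also feed the cost-effectiveness model, so an interval that is too narrow would understate the uncertainty behind the national recommendation.

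**Working it through.** **Inputs from the protocol article.** n = 315 women per strategy; adherence p = 0.70; difference 10 points; alpha 0.05 (taken as two-sided; the article does not say); power 80%. Units per region: 1 hospital + 3 to 5 practices = 4 to 6. Professionals per region: 10 + 5 + (8 to 10) = 23–25 midwives and obstetricians, or 28–30 with the five paediatricians. Treatment of the baby is a key component of adherence, so the larger count is also relevant.

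**Assumed.** The ICC, over 0.01–0.10; equal cluster sizes; roughly one main provider per woman.

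**Step 1: the plan's own figures.** Half-width = 1.96 × √(0.70 × 0.30 / 315) = 5.06 points, so 64.9–75.1% (Wilson: 64.7–74.8%). Both round to 65–75%, with a design effect of 1.

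For 70% v 80%, the usual two-proportion formula needs 294 per group, or 313 with continuity correction, so 315 fits. Power at 315 is

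Φ{[0.10 × √315 − 1.96 × √(2 × 0.75 × 0.25)] / √(0.21 + 0.16)} = Φ(0.94) = 83%.

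This is the favourable direction: the same n gives 75% for 70% v 60%.

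**Step 2: allow for clustering.** Design effect DE = 1 + (m − 1) × ICC, with m = 315 / number of clusters. Half-width = 5.06 × √DE. Power uses the formula above with 315/DE in place of 315.

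Example: 24 providers, ICC 0.05. m = 13.1; DE = 1 + 12.1 × 0.05 = 1.61; effective n = 196; half-width = 5.06 × √1.61 = 6.4 points; power = Φ(0.33) = 63%.

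| Clustering | ICC | DE | Half-width (points) | Power, 70 v 80 |
|---|---|---|---|---|
| none (as planned) | 0 | 1 | 5.1 | 83% |
| 30 to 24 providers | 0.01 | 1.10–1.12 | 5.3–5.4 | 79–78% |
| 30 to 24 providers | 0.05 | 1.48–1.61 | 6.1–6.4 | 67–63% |
| 30 to 24 providers | 0.10 | 1.95–2.21 | 7.1–7.5 | 55–50% |
| 6 to 4 units | 0.01 | 1.52–1.78 | 6.2–6.7 | 65–59% |
| 6 to 4 units | 0.05 | 3.58–4.89 | 9.6–11.2 | 33–26% |

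The provider and unit rows are alternative descriptions and are not to be added. They use the normal quantile. With so few units a t quantile is more honest: at ICC 0.05 it gives ±12.5 points for 6 units and ±18.2 for 4.

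**Step 3: how much clustering the figures tolerate.** Power of 80% needs 294 effective women, so DE may not exceed 315/294 = 1.071. The ICC may then be at most 0.071/12.1 = 0.006 (24 providers) to 0.071/9.5 = 0.007 (30 providers), and about 0.001 by unit (0.071/51.5 for 6 units, 0.071/77.8 for 4). The half-width passes 5.5 points at an ICC of about 0.016–0.019 for 25–30 providers and 0.002–0.004 for 4–6 units.

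**The case against.** Several counter-arguments carry weight.

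- **The calculation is correct.** It is. The fault lies in the independence assumption.
- **The providers are a census.** All members of a participating region must take part, so for adherence among those very professionals the variation between them need not widen the interval. That holds for a purely local statement. It does not rescue the figure for a study meant to support national recommendations.
- **The ICC is unknown and may be small.** No value is given, and training is meant to bring providers to the same level, so the variation found earlier does not fix the post-test ICC. At a provider ICC of 0.01 the interval hardly changes. The power margin is much thinner (step 3).
- **One woman may be cared for by several professionals** in pregnancy, in labour and after birth. So 10 to 13 women per provider is only an approximation.
- **Completeness of use is a share of activities.** Scored per woman, its standard deviation could be below the binary √0.21 = 0.458, which would partly offset the widening. The sample-size section does not use such a score.

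A reader might also infer that pre-test to post-test differences will look significant too often. The article does not support that. The same regions and largely the same providers appear in both periods, so stable provider effects largely cancel in the difference; only provider-by-period variation would inflate the error. Nor can one infer that the final analysis will ignore clustering: the article names regression only in general terms, and the model may be specified elsewhere.

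**Conclusion.** The point holds against the planning statement. The 65–75% interval and the 80% power are properties of 315 independent women, and the article's own definition of adherence and description of the regions contradict that independence. Both are too favourable when results are carried beyond these providers. The loss is slight for precision at a provider ICC of 0.01, clear at 0.05, and large if practices or hospitals differ even modestly.

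The size rests on assumed ICCs, equal clusters, about one main provider per woman, and adherence treated as a binary outcome. The matter is separate from having a single region per strategy: that confounds strategy with region, and no design effect within a region repairs it.

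**What to change.** 1. Restate the interval and the power together over a stated ICC range, at provider and at unit level. For example, 315 women at 70% adherence give about 64–76% at a provider ICC of 0.05 (power 63–67% for 70% v 80%), and about 60–80% with six units or 59–81% with four at a unit ICC of 0.05 (power 26–33%). Alternatively, say plainly that the published figures hold only under independence and only for the participating regions' own providers.
2. Add provider and practice codes to the existing standardised registration form.
3. Report cluster-adjusted intervals for the adherence percentages, with a small-sample correction. A random practice effect need not be insisted on, since four to six units per region estimate it poorly.
4. Carry these wider intervals into the sensitivity analyses of the cost-effectiveness model.

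The cost is a less favourable stated precision and power, one or two extra fields on a form, and a little more analysis. No extra women are needed to state the precision and power honestly; regaining 80% power would be a separate decision.

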## Discussion

The effective prevention of EOGBS will be the product of the efficacy of the applied prevention strategy (to what extent can the strategy in itself prevent EOGBS) and the level of implementation (to what extent is the strategy adhered to by all care providers and all pregnant women). Since improved adherence may enhance EOGBS prevention, our study focuses on determinants that affect adherence to three prevention strategies in daily practice. The empirical data about adherence will be used to assess the cost-effectiveness of each strategy in daily practice.

Although the results will primarily be used for the national implementation of the most cost-effective strategy in the Netherlands, the results could be of interest to health-care professionals, policymakers and insurance companies in other countries. Regardless of the prevention strategy used, we expect that other countries will also have problems with actual adherence. Our determinant analysis found a variation in adherence to several recommendations of the guideline, especially in the assessment of clinical risk factors and culture-taking procedures. In the United Kingdom also, considerable variation in the management of EOGBS risk prevention was recently reported, including the application of risk factors and the choice of antibiotics [35].

Our study has some limitations. Due to the low prevalence of EOGBS, a clinical effect study for the detection of a statistically significant difference in the prevalence of EOGBS is not feasible. Our study will use the incidence of neonatal colonisation as a proxy measure for implementation. A second limitation is that the results may be affected by regional variations. To overcome this problem we will include regions with minimal differences in the organisation of maternity care (OCGs) and population characteristics.

We expect the results of our study to contribute significantly to the national and international re-evaluation of the best strategy for the prevention of EOGBS.

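### With one region randomised per strategy, the stated 80% power for a 10-point adherence difference between strategies is not available; it holds only for a difference between these three particular regions.

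*Protocol article*

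**What the plan says.** Under Activity 1, Participants, the design is fixed: "Three OCG regions will be recruited. Each OCG consists of one hospital working with three to five midwifery practices". One of the three prevention strategies "will be randomly allocated to each region". The randomised unit is therefore the region, and each strategy has one.

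The Sample size section gives two reasons for 315 women. The first is precision: "in the case of 70% adherence, the 95% confidence interval will be 65-75" per cent. The second is a comparison: "this number will ensure statistical significance at a variation in adherence of 10% between strategies (alpha = 0.05, power = 80" per cent. The post-test then takes 315 women per region (945 in all) and the pre-test 105 per region (315 in all). The section gives no ICC and no design effect.

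The Analysis section keeps each region with its allocated strategy, takes pre-test to post-test differences into the cost-effectiveness analysis, and names descriptive and regression techniques. The Discussion lists regional variation as a limitation and answers it so: "To overcome this problem we will include regions with minimal differences in the organisation of maternity care (OCGs) and population characteristics".

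**The concern.** The power statement concerns differences between strategies, but every such difference is a difference between two single regions. Adding women narrows the estimate for each region. It does not show how far two regions would differ under the same strategy, and with one region per strategy there are zero degrees of freedom for that variation. An analysis plan written later cannot supply the missing replication.

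Zero regional variation is not a safe default here. The article describes adherence as depending on providers, logistics and organisation, and its training section reports considerable variation among care providers in how cultures are taken.

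The study is meant to support a national recommendation, with adherence feeding the cost-effectiveness model. A 10-point gap between two regions, read with the assurance of 80% power at a 5% level, could be taken for a strategy effect when it is partly or wholly regional.

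**Working it through.** **Inputs from the article:** 3 regions, 1 per strategy; 315 women per region post-test and 105 pre-test; alpha 0.05 (taken as two-sided); power 80%; reference adherence 70%; difference 10 points. **Assumed:** ICC from 0.001 to 0.05, since none is given.

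**1. The article's own figures.**
- Half-width of the interval: 1.96 × √(0.7 × 0.3 / 315) = 0.0506, so 65–75% is right.
- 70% v 80%: n = [1.96√(2 × 0.75 × 0.25) + 0.842√(0.21 + 0.16)]² / 0.10² = 294 per arm, or 313 with continuity correction. At 315 per arm, power without the correction is 82.8%.
- In the other direction (70% v 60%), 356 per arm would be needed (376 with correction), and 315 gives 75.0%. The point does not depend on this.

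So 315 is a sound figure for women who are independent and individually allocated.

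**2. What the randomisation can support.** Three strategies over three regions give 3! = 6 allocations. If these are equally likely, a randomisation test of one pair of strategies cannot give a two-sided p-value below 2/6 = 0.33 (one-sided 1/6 = 0.17), whatever the data show.

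**3. Size under assumed ICCs.**
- Design effect: DE = 1 + (315 − 1) × ICC.
- Effective number of women per arm: 315 / DE.
- True type I error of a test that ignores region: 2 × [1 − Φ(1.96 / √DE)].
- Power for 70% v 80% if the ICC were known from outside: Φ[(0.10 − 1.96 × SE₀) / SE₁], with SE₀² = 2 × 0.75 × 0.25 × DE / 315 and SE₁² = (0.21 + 0.16) × DE / 315.

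| ICC (assumed) | DE | Effective n per arm | True type I error, region ignored | Power, ICC known |
|---|---|---|---|---|
| 0 | 1 | 315 | 5% | 83% |
| 0.001 | 1.31 | 240 | 8.7% | 72% |
| 0.005 | 2.57 | 123 | 22% | 44% |
| 0.01 | 4.14 | 76 | 34% | 30% |
| 0.05 | 16.7 | 19 | 63% | 10% |

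An ICC of 0.01 at 70% adherence is a between-region standard deviation of √(0.01 × 0.21) = 4.6 points. The power column is generous, because this trial cannot estimate the ICC.

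**4. Does the pre-test restore the power?** Compare the change in one region with the change in another, with independent women and all cells at 70% except one post-test cell at 80%. Then SE = √(2 × 0.21/105 + 0.21/315 + 0.16/315) = 0.072, and power is Φ(0.10/0.072 − 1.96), about 28%. This is before any allowance for regions changing differently over time.

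**The case against.** The best defence is the pre-test. Every region is first measured under the same Dutch guideline, so stable differences in baseline adherence can be seen and allowed for. That stands. A reader might infer that strategy and region cannot be told apart in any respect, and the article does not support that reading. What stays confounded is narrower: regional change between the two periods, and how well each region takes up what it is given.

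The pre-test does not rescue the power statement, however. The Adherence section measures the Dutch guideline in the pre-test and the allocated strategy in the post-test. In two regions the list of prescribed activities therefore changes; for example, only the combination strategy requires the culture at 35–37 weeks. A difference in differences on overall adherence would mix the strategy effect with a change of yardstick, and step 4 shows that it is also imprecise.

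A reader might also infer that the trial will report an unadjusted two-proportion test between regions. The Analysis section does not say so. The type I errors above show what such a test would do; they do not describe a stated plan.

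It is fair to add that precision is the first purpose given for 315, that the regions are called pilot regions in the Abstract, that the inclusion criteria restrict their structure, that the cost model already has sensitivity analyses, and that regional variation is disclosed. These points limit the damage. They do not make the between-strategy claim true, and choosing similar regions can neither remove nor measure the variation that remains.

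**Conclusion.** The concern holds for two statements: the between-strategy significance and power claim in the Sample size section, and the Discussion's assertion that selecting similar regions overcomes regional variation. The arithmetic behind 315 is correct; the fault lies in what it is said to deliver. It gives about 80% power for a difference between these three regions with women treated as independent, and no defined power for a difference attributable to strategy.

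The lack of replication follows from the design alone and matters at any ICC above zero. Its size rests on the assumed ICCs. At 0.001 the loss is moderate (type I error about 9%, power about 72%); at 0.01 it is severe (about 34% and 30%). The article does not say which value applies, and the trial cannot estimate it.

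**What to change.** - **Sample size:** keep 315 women per region as the basis for within-region precision (70%, 95% CI 65–75%). Delete the claim of significance and 80% power between strategies. State that between-strategy contrasts are descriptive, because strategy is confounded with region.
- **Discussion:** replace the statement that similar regions overcome the problem with one that regional confounding is at best reduced and remains a limitation.
- **Cost-effectiveness sensitivity analyses:** vary the between-strategy adherence differences over a stated range of between-region variation.
- **Use of the pre-test:** report pre-to-post change relative to the Dutch-guideline region descriptively only, and only for outcomes or adherence components defined identically in both periods, such as risk-factor assessment and neonatal colonisation.

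The cost is a change of wording and some added sensitivity analysis, with no extra regions or women. The downside is that the stated power is withdrawn and the uncertainty shown is wider.
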